### **5.4 Subject Log**

If possible, the investigator must record the reason and the exact time of the premature discontinuation of treatment in the case report form (CRF). If more than one reason is given, the investigator must indicate the main reason.

In case of treatment discontinuation for any reason between visits T0 and T2, an end-of-study visit should be done with all the assessments planned for the follow up as early as possible after the treatment study discontinuation.

## 6. Outcomes, predictors and mediators

For description of the measurements employed, see section 7. For overview of the times of measurements, see Table 1 (appendix).

#### 6.1.2 Changes in diagnostic status

Diagnostic status according to the DSM-5 criteria for OCD at baseline and 3, 12 months and 5 years follow-up will be employed. The Structured Clinical Interview (SCID) for DSM-5 Axis I disorders will be employed (63).

### 6.2 Secondary Endpoints

#### *Self-report measures*

Measures of anxiety, depression, global functioning, severity of the disorder, self-reported OCD-symptoms, SUD-measures, quality of life, changes in work and social status as well as changes in medication and use of health care will be included as secondary end-points related to the main objective of the study. For description of instruments, see section 7 and Table 1 in the Appendix.

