### 5.2 Exclusion Criteria

#### *Exclusion criteria related to the ERP*

- OCD symptoms primarily associated with hoarding
- Ongoing substance abuse/dependence
- Bipolar disorder or psychosis
- Ongoing/ planned suicidal ideation
- Mental Retardation, based on previous medical history
- If using antidepressants:
  - Not on stable dosage 12 weeks before the intervention
  - Unwilling to remain on stable dosage during the four intervention days

- Unwilling to refrain from anxiety reducing substances, such as anxiolytics (e.g. benzodiazepines) and alcohol during the two days of exposure.
- Patients living > 1 hour drive by car/ train from the treatment location.

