## **7.2 Self-report questionnaires**

### **7.2.1 Self-report of symptoms and disorders**

- *Obsessive-Compulsive Inventory – Revised* (OCI-R) (91). The OCI-R is an 18 items self-rating scale, measuring six different symptom dimensions of OCD. The OCI-R total score has high test-retest reliability and high sensitivity to change, in relation to the Y-BOCS (92).
- *Dimensional Obsessive Compulsive Scale Short-Form (DOCS-SF)* is a self-report questionnaire adapted from DOCS (93). It consists of a symptom checklist covering obsessive and compulsive thoughts about “contamination”; “responsibility for harm, injury or bad luck”; “unacceptable obsessional thoughts”; “symmetry completeness and exactness”. For all dimensions five items on scale from 0 to 8 assesses severity: (a) time occupied by obsessions and compulsions, (b) avoidance behavior, (c) associated distress, (d) interference with daily functioning, and (e) difficulty disregarding obsessions and refraining from the compulsions. Item A and E is split into two questions. The total score ranges from 0 to 40.
- *Generalized Anxiety Disorder Assessment 7* (GAD-7) (94-96) is a brief 7-item self-report measure for generalized anxiety symptoms. Although developed for measuring severity of generalized anxiety disorder, the GAD-7 measures severity of general anxiety symptoms common to several anxiety disorders. The GAD-7 has been demonstrated to have good psychometric properties.
- *Patient Health Questionnaire*, (PHQ-9) (98-101) is a 9-item self-report questionnaire measuring level of depressive symptoms. Items are scored on a scale from 0 (not at all) to 3 (nearly every day). The PHQ-9 has been validated for clinical use and shows sound psychometric properties with high test-retest reliability.
- *The Bergen Insomnia Scale* (BIS) (77) will be used to screen for sleep disturbances. The scale has six items covering different aspects of sleep disturbances the past 4 weeks. The scale has acceptable psychometric properties (77)
- *Record of concomitant drug/medication* use during the period of the study will be recorded on a specially designed sheet.

- *Nijmegen Motivational List 2 (NML-2)* is a 25-item questionnaire assessing how the disorder impacts on the patients, motivation for treatment and beliefs about the present form of therapy. It has acceptable psychometric properties (105).

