### 7.2.3 Personal characteristics

- *The Client Socio-Demographic and Service Receipt Inventory (CSSRI)* (102) records socio-demographic data as well as previous treatment history. This is a comprehensive self-report measure which registers service utilization and cost of treatment for people with mental disorders.
- *Number of previous treatments* is a worksheet asking the patient to fill out information about any previous treatments for OCD, and the characteristics of the previously received treatments.
- *Onset and duration of disorder* is a specially designed worksheet where the patients record the onset and duration of his/her OCD.

- *Personality Inventory for DSM-5 Brief Form (PID-BF)* is a recently developed personality inventory, which is aimed at assessing dimensions in personality and personality disorders (110).
- *The Warwick-Edinburgh Mental Well-being Scale (WEMWBS)* (104) will be administered to assess mental well-being. This scale has 14 items covering different aspects of mental health related to mental well-being. The WEMWBS has shown good psychometric properties.
- *The Work and Social Adjustment Scale (W & SAS)* (103) is a short questionnaire measuring work status and social adjustment. The scale has good psychometric properties.
- *The Highly Sensitive Person Scale (HSPS)* (80) is a self-report questionnaire which measures aspects of sensitivity towards internal and external stimuli. The psychometric properties of the scale have been evaluated, demonstrating the scale's reliability and validity.
- *The Dispositional Resilience Scale – Revised (DRS-15-R)* (79) is a 15-item self-report instrument measuring resilience to challenges and life-stress. The Norwegian version of the instrument has good psychometric properties (111).
- *The Brief Illness Perception Questionnaire (BIPQ)* (78) will be administered to record illness perception. Although originally developed for measuring perception of somatic illness, the BIPQ has also been adapted to measure perceptions of mental health. The scale has sound psychometric properties.

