### 11.2 Treatment Assignment/ Randomization

Patients are upon inclusion randomly assigned to DCS or placebo using a 2:2:1 ratio of 250 mg DCS: 100 mg DCS: placebo. In order to control for potential interaction effects with antidepressants (121), patients will be stratified on current anti-depressive medication or not. Within each subgroup patients will be randomized in blocks of 5 into ERP+DCS 100 mg, ERP+DCS 250 mg, or ERP + Placebo in the proportions 2:2:1.

A research unit at Karolinska Institute, Sweden, which is not involved in the study, will be responsible for the randomization. Randomization lists will be sent directly to Kragerø pharmacy that will be responsible for providing the medication for patients enrolled.

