## APPENDIX

**Table 1. Measurements employed in the study**

| Description                                                                         | T0
Pretreatment/
baseline | During
treatment | T1
One week
post
treatment | T2
3 months
post
treatment | T3
One year
post
treatment | T4
5 years post
treatment |
|-------------------------------------------------------------------------------------|---------------------------------|---------------------|-------------------------------------|-------------------------------------|-------------------------------------|---------------------------------|
| Informed consent                                                                    | X                               |                     |                                     |                                     |                                     |                                 |
| Inclusion/exclusion
evaluation                                                   | X                               |                     |                                     |                                     |                                     |                                 |
| Adverse event                                                                       |                                 | X                   | X                                   | X                                   | X                                   | X                               |
| Assessor administrated instruments                                           |                                 |                     |                                     |                                     |                                     |                                 |
| SCID-I                                                                              | X                               |                     |                                     | X                                   | X                                   | X                               |
| Y-BOCS interview                                                                    | X                               |                     | X                                   | X                                   | X                                   | X                               |

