| DOCS-SF                                                                             | X                               | X                   | X                                   | X                                   | X                                   | X                               |
| PHQ-9                                                                               | X                               | X                   | X                                   | X                                   | X                                   | X                               |
| BIS                                                                                 | X                               |                     | X                                   | X                                   | X                                   | X                               |
| Record of
concomitant
drug/medication                                         |                                 |                     | X                                   | X                                   | X                                   | X                               |
| Y-BOCS checklist                                                                    | X                               |                     |                                     |                                     |                                     |                                 |
| NML-2                                                                               | X                               |                     |                                     |                                     |                                     |                                 |
| Personal characteristics                                                     |                                 |                     |                                     |                                     |                                     |                                 |
| CSSRI                                                                               | X                               |                     |                                     | X                                   | X                                   | X                               |

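### Change in medication is a secondary endpoint, but the medication record is not scheduled at T0, so most drugs and all doses lack a stated pre-treatment value

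*Protocol*

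**What the plan says.** Section 6.2 of the Protocol lists the secondary endpoints, and among them "changes in medication and use of health care will be included as secondary end-points". For the means of measurement it says: "For description of instruments, see section 7 and Table 1 in the Appendix".

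Section 7.2.1 describes one instrument for drugs taken. It is a record of concomitant medication whose "use during the period of the study will be recorded on a specially designed sheet". In Table 1 of the Appendix the row "Record of concomitant drug/medication" is ticked at T1, T2, T3 and T4. The column headed "T0 Pretreatment/ baseline" is blank for that row, as is the column for the treatment days.

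Three other places imply some knowledge of medication before dosing:

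- Section 11.2: "patients will be stratified on current anti-depressive medication or not".
- Section 5.2, among the exclusions for antidepressant users: "Not on stable dosage 12 weeks before the intervention".
- Section 7.2.3 describes the CSSRI, ticked at T0, T2, T3 and T4. It covers socio-demographic data and treatment history, and "registers service utilization and cost of treatment for people with mental disorders".

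Section 11.4 deals with concomitant and prior medication. It sets restrictions for the exposure days but schedules no record.

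**The concern.** An endpoint worded as change needs a value from before treatment, taken in the same terms as the later values. The record that serves this endpoint starts one week after treatment, so as scheduled it can show change only from T1 onwards. T1 is a poor substitute for baseline. It follows randomisation and dosing, so it may already reflect treatment, and it closely follows a required pause in anxiolytics.

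What is at stake is whether the trial can say that patients reduced, stopped, switched or started drugs relative to their state at entry. An analysis plan can define the change variable later, but it cannot supply data that the visit schedule never collected.

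**Working it through.** No arithmetic applies. The check sets the endpoint against each source that could supply a pre-treatment value.

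**Step 1: the endpoint's own instrument.** Table 1 for the medication record reads: T0 blank, during treatment blank, T1 X, T2 X, T3 X, T4 X. Table 1 places T1 one week after treatment. The capsules are taken on Days 2 and 3 of the four-day course (sections 8.6 and 9.6). The first scheduled entry therefore follows both doses.

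**Step 2: is the blank a pattern or an exception?** In the Table 1 block of symptom self-reports, every other row has a T0 tick: OCI-R, GAD-7, DOCS-SF, PHQ-9, BIS, the Y-BOCS checklist and NML-2. The medication record is the only row in that block without one. This looks like an oversight.

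**Step 3: other sources before dosing.**

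| Source | What the Protocol says it holds | What it gives at baseline |
|---|---|---|
| Stratification factor (11.2) | Antidepressant use, yes or no | One class; no drug name or dose |
| Eligibility form (7.1; T0 in Table 1) | A checklist of the inclusion and exclusion criteria | Antidepressant dose stability; not stated to record drug or dose |
| CSSRI (7.2.3; T0 in Table 1) | Socio-demographics, treatment history, service use, cost | A baseline for health care use; current drugs not mentioned |
| Interview on latest treatment course (7.1; T0) | Experience of the previous treatment and timeline of relapse | Not stated to list current drugs |
| Worksheet on previous treatments (7.2.3; T0) | Earlier OCD treatments and their characteristics | Not stated to list current drugs |

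**Step 4: what can be computed.** Starting or stopping an antidepressant after entry can be derived from the stratification factor and the later records. Change of antidepressant drug or dose, and any change in another class, has no stated pre-treatment value.

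**Step 5: are other classes relevant?** Section 5.2 excludes patients who will not refrain from anxiolytics on the exposure days, and section 11.4 restricts use on those days. Neither bars regular users from enrolling. Anxiolytic use at entry is therefore possible, and no record of it is scheduled.

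**Step 6: the other half of the phrase.** Use of health care has a T0 assessment through the CSSRI. The gap concerns medication only.

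**The case against.** The strongest reply is that baseline information does exist. Antidepressant use must be known before randomisation, and stability of the dose over the preceding 12 weeks is an eligibility condition. This stands. A reader might infer from the blank T0 cell that there is no medication baseline at all; the Protocol does not support that. For antidepressants a coarse baseline is available.

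A reader might also infer that the antidepressant interaction is undermined. It is not. The factor is yes or no, it is fixed at randomisation, and no analysis by antidepressant drug or dose is stated.

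Nor does the blank treatment-days column show that drug use on the exposure days goes unrecorded. The sheet covers use over the study period, and nothing stops the T1 entry from looking back over those days.

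The CSSRI may contain questions on current drugs. The instrument itself is not available here, so this can be neither confirmed nor excluded. What stands is that the Protocol does not say so, and does not name the CSSRI as the source for this endpoint.

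Finally, the definition of the change variable may properly be left to the analysis plan. That is accepted, but it does not answer the point: the visit schedule decides which values exist.

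**Conclusion.** The point holds in a limited form. The only instrument described as recording medication has no T0 assessment, and the Protocol names no other baseline source for drug, dose or classes other than antidepressants. As scheduled, the endpoint in section 6.2 can be computed from a pre-treatment value only as starting or stopping an antidepressant.

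The gap affects every patient but only this one secondary endpoint. The primary endpoint, the sample size and the stratified antidepressant comparison are untouched. The documents give no basis for putting a number on any resulting bias, and none is claimed.

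The conclusion rests on two assumptions: that Table 1 states the full schedule of the medication record, and that the T0 forms hold no more than the Protocol says they do. If the CSSRI or the eligibility form in fact lists current drugs and doses, the gap shrinks to a failure to name the source.

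**What to change.** In Table 1, add an X at T0 for the concomitant medication record, capturing drug, dose and start date. In section 6.2, define the endpoint as change from T0.

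The cost is one existing form completed at one more visit, plus an amendment to Table 1 and one sentence in section 6.2. Patients already complete other self-reports before treatment (section 9.5), so no new visit is needed. No clinical rule changes. The tick should be in place before patients are enrolled, because a T0 value not collected at the time could only be reconstructed afterwards.

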#### *Behavioral test*

The exposures during treatment will follow a specific procedure training the patient to "lean into the anxiety" (LET-technique, see description of instruments). The first and last exposure during the two treatment days will be videotaped and changes in patients behavior as well as self-reported anxiety scores and "holding back"-scores will be compared.

### 6.3 Predictors

The following variables will be employed as predictors of outcome: the patients' evaluation of the credibility of the treatment (73), presence of comorbidity (74, 75), number of previous

treatments, treatment motivation as well as the onset, duration and severity of the disorder. For description of instruments, see section 7. For assessment points see Table 1 in the Appendix.

#### **6.4 Mediators**

The working alliance, score of LET intervention during sessions as evaluated by the patient (76), within session reduction of anxiety, treatment evaluation, as well as compliance with homework after the treatment will be employed as mediators. For description of instruments, see section 7. For assessment points see Table 1 in the Appendix.

#### **6.5 Descriptives**

Please note that patients in the current trial are entitled to treatment in the Norwegian specialist health care, and that the questionnaires listed below are part of standard diagnostic and assessment procedures in the OCD-team in Helse-Bergen, and are approved as part of the current trial by the Regional Committee of Ethics (2013/195/REK Sør-Øst- D). The following are routinely measured: sleep disturbances (77); the patients' beliefs about the stability of the condition (78); stable personality characteristics (79); sensitivity to sensory and external stimulation (80); and Behavior Rating Inventory of Executive Function – Adult Version (82). For description of instruments, see section 7. For assessment points see Table 1 in the Appendix.

### **7. Description of the measurements employed**

#### **7.1 Assessor administrated measurements.**

- *The Mini-International Neuropsychiatric Interview* (M.I.N.I.) (83) is a brief structured diagnostic interview, administered by a clinician, covering Axis I diagnoses in DSM-IV and ICD-10. The M.I.N.I. has been reported to have good psychometric properties (84).
- *Inclusion/exclusion evaluation*: A study specific CRF summarizing all inclusion and exclusion criteria. The form is to be used as a checklist by the clinician.
- *Structural Clinical Interview for DSM Disorders* [SCID-I (75, 85, 86)] cover Axis I psychiatric disorders according to DSM-5.
- *Yale-Brown Obsessive-Compulsive Scale* (Y-BOCS) (87). The Y-BOCS is regarded as the gold standard for assessing the severity of OCD symptoms. It consists of a symptom checklist covering obsessions and compulsions and a severity scale (88). The severity scale comprises 10 items, rated on a 5-point Likert scale ranging from 0 (no symptoms) to 4 (severe symptoms). The total score ranges from 0 to 40 and consists of sub scores for obsessions (range 0 to 20) and compulsions (range 0 to 20). Y-BOCS has excellent inter-rater reliability and moderate to good internal consistency. The Y-BOCS consists of both a clinical interview and self-report scale (87).
- *Global Assessment of Functioning* (GAF) (89) is used to evaluate global improvement in both symptoms and functioning. The range on each scale is from 0-100, with higher scores indicating better functioning.
- *The Clinical Global Impressions Scale* (CGI-I) (90). The CGI is a 8-point scale that requires the clinician to rate the severity of the patient's change/relapse at the time of assessment relative to the subjects condition after last treatment (baseline), with following

alternatives 0=Not assessed, 1 =Very much improved, 2 =Much Improved, 3=Minimally Improved, 4=No change, 5=Minimally worse, 6=Much worse, 7 =Very much worse

- *Evaluation of the treatment* is recorded (the therapist interviews the group members together) the last treatment day on covering different aspects of treatment satisfaction (16).
- *Anamnestic information and interview regarding latest treatment course*. Consists of a short relapse interview on how the previous treatment as well as the time after treatment was experienced by the patient, as well as a timeline for relapse.
- *CORE* Problem-specific therapist competences describe the knowledge and skills needed when applying CBT principles for OCD. Developed by Steketee, Foa and Kozak.

